**3.2.3. Point out potential problems and limitations**

Including patients with a full range of cardiac surgery procedures (e.g. CABG, aortic- or mitral valvular surgery, combined valvular and CABG surgery, and combination of ascending aortic aneurysm surgery, valvular or CABG surgery) might result in heterogeneous data with high variance. However, our proposed study population reflects a large group of patients with increased risk of perioperative morbidity and mortality.

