**3.1.2 Background**

**Medical problem:** Cardiac surgery with CPB remains one of the most common surgical procedures, performed in about 1.5 million patients worldwide each year. Although surgical outcome has improved over time ^1^, increasingly older patients with multiple co-morbidities still remain at high risk for perioperative morbidity and mortality due to intraoperative impairment of vital organ perfusion and oxygenation. Moreover, cardiac surgery is generally associated with a predictable incidence of myocardial, neurological and renal dysfunction that accounts for significant morbidity and mortality of up to 10% depending on age, sex, co-morbidities and complexity of surgical procedures ^2-5^.

Postischaemic myocardial dysfunction after cardiac surgery is attributable to a multi-factorial aetiology, e.g. myocardial stunning, apoptosis, MI and ischaemia-reperfusion-induced injury. Clinically low cardiac output and hypotension requiring inotropic support are common findings. With respect to CABG alone, 16% of patients may experience myocardial infarction, severe ventricular dysfunction, heart failure, and/or death despite advances in surgical technique, CPB, and anaesthesia ^6^.

In addition, brain injury after CPB remains a common and serious complication ^7^. According to the ACC/AHA guidelines ^5^ postoperative neurological deficits can be classified into type 1 injuries, which are predominantly focal stroke, transient ischaemic attack, and fatal cerebral injuries in 3-5 % of patients due to macroembolism, and type 2 events, which reflect a more global/diffuse injury, with disorientation, agitation and postoperative neurocognitive dysfunction (POCD). POCD has been reported in 30 to 79% of patients at discharge and 24% to 57% at 6 months ^8^. Embolic events, changes in cerebral blood flow, global hypoperfusion, cerebral reperfusion injury, and a CPB-triggered whole body inflammatory response represent possible mechanisms for the high incidence of POCD. Elderly patients are more susceptible to cognitive impairment and stroke after cardiac surgery than others ^9^. Thus, with the increase in the percentage of elderly patients undergoing cardiac surgery, there has been a parallel increase in the incidence of stroke and POCD ^10^. Further, neurological injury negatively impacts the patient’s quality of life and health resources.

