**3.2. Methods**

**3.2.1. Describe data collection techniques.**

**3.2.1.1. Co-workers**

-> Names in brackets indicate the role of each person involved in the project

- Dr. [name] (PM), PD Dr. med. [name] (BB), PD Dr. ret. nat. [name] (MA), [name]. med. [name] (JS); Department of Anaesthesiology and Intensive Care Medicine, University Hospital Schleswig-Holstein, Campus Kiel, Germany
- Prof. [name] (JC); Department of Heart and Vascular Surgery, University Hospital Schleswig-Holstein, Campus Kiel, Germany
- Prof. [name] (KDZ); Department of Anaesthesiology and Intensive Care Medicine, University Frankfurt, Germany

**3.2.1.2. Clinical procedures (PM, BB, JS, JC):** One-hundred eighty patients undergoing cardiac surgery (single CABG, aortic- or mitral valvular surgery, combined valvular and CABG surgery, and combination of ascending aortic aneurysm surgery, valvular or CABG surgery) will be included. Thus, study population reflects a large group of patients with increased risk of perioperative morbidity and mortality. Following exclusions criteria will be defined: Emergency cases, myocardial infarction (MI) up to 7 days and stroke up to 2 months prior to enrolment, age below 18 years, off-pump heart surgery, renal failure, drug therapy with sulfonamide and nicorandil, ejection fraction less than 30%, and previous psychiatric and neurological illness. All patients will receive standard perioperative care. The applicant (PM) will inform the patient about the nature of the trial, its aims, expected advantages as well as possible risks. Each patient must consent in writing to participate in the study. The informed consent will be signed by both patient and treating investigator.

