Patients will be randomly assigned to receive either control intervention or RIPC before CPB. RIPC will be induced during anaesthesia by four 5-min cycles of right upper limb ischaemia and 5-min reperfusion using a blood-pressure cuff inflated to 200 mmHg (at least to a pressure 15 mm Hg greater than the systolic arterial pressure) measured via the arterial line ^17,23,28^. Control patients undergo sham placement of the blood pressure cuff around the upper limb with inflation to 20 mmHg. Upper limb ischaemia provided by blood-pressure cuff inflation will be performed by a single study assistant, and will be blinded to the anaesthesia team, cardiac surgeon and the patient. The anaesthesia team will perform standardised anaesthesia in all patients.

Midazolam 3.75-7.5 mg will be given orally to every patient 1 h before surgery. On arrival in the anaesthetic room, a peripheral venous and an arterial cannula will be inserted before anaesthesia. Anaesthesia will be induced with propofol (2 mg/kg), sufentanil (0.1 μg/kg), and rocuronium (0.6 mg/kg). The trachea will be intubated and mechanical ventilation will be started with oxygen with room air to achieve an end-tidal carbon dioxide tension of 4–5 kPa. Before cardiopulmonary bypass, anaesthesia will be maintained with propofol (≈ 4-6 mg/kg/h) and sufentanil (≈ 0.5-1.5 µg/kg/h). A 7F saline filled catheter will be inserted in the right internal jugular vein for determination of central venous pressure and drug administration. Arterial blood pressure, leads I and II of the electrocardiogram, and nasopharyngeal temperature will be recorded continuously. Standard CPB techniques with blood cardioplegia will be used.

Transesophageal echocardiographic variables (E/A-Ratio, left ventricular ejection fraction) will be subsequently obtained at baseline, after RIPC, and after 15 and 30 min after CPB (BB). Cardiac MRI is aimed to be performed preoperative, 5-7 days and 3 months postoperative to analyze right and left ventricular performance ^29,30^.

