**3.2.2. Describe types of data to be obtained and statistical or power analysis if indicated**

The sample size calculation is based on the assumptions that the incidence of cognitive decline at 5-7 days postoperative is 30% after on-pump surgery ^36-38^, and that one-third reduction could be achieved using RIPC. Individual patients may decline intra-hospital study follow up. We estimated loss to follow up as 5 % of the patients based on previous experience for clinical studies in our hospital. A total of 90 patients per group were estimated.

Secondary endpoints will be analysed in an exploratory way by standard statistical methods for comparing independent samples with respect to their measurement level and/or type of distribution (parametric and nonparametric methods).

With respect to feasibility of recruitment, the intended recruitment rate is based on a prospective recording of all potentially included patients from October to December 2008 in our institution. Each week a mean of eight patients fulfilling the inclusion criteria could be included. Thirty percent of these patients were estimated to give informed consent regarding study participation corresponding to two to three patients per week. Based on 52 weeks of recruitment per year and one study team (one anaesthetist, one nurse) available we calculated a realistic enrolment of 140 patients per year.

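### The protocol flags its procedure mix as a possible source of high variance but names no stratified or blocked randomisation and no covariates for the secondary comparisons: a modest, cheaply corrected weakness in balance and precision, not a bias

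*Protocol*

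**What the plan says.** Section 3.2.1.2 sets the size and range of the trial: "One-hundred eighty patients undergoing cardiac surgery", from isolated CABG through single valve operations to ascending aortic surgery combined with valve or CABG procedures. The only age limit is a minimum of 18 years.

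Section 3.2.3 gives one limitation, that this range "might result in heterogeneous data with high variance". Its reply is that the population represents a sizeable group at raised risk. That speaks to relevance, not to variance.

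Section 3.1.2 states that morbidity and mortality from myocardial, neurological and renal dysfunction depend on age and complexity of the operation, among other factors. On cognition it adds: "Elderly patients are more susceptible to cognitive impairment and stroke after cardiac surgery than others".

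The allocation text in 3.2.1.2 is a single sentence: "Patients will be randomly assigned to receive either control intervention or RIPC before CPB". It mentions no stratification, blocking or minimisation.

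Section 3.2.2 states no test for the primary endpoint. For the secondary endpoints it plans exploratory two-sample methods, parametric or nonparametric according to the type of data, and names no covariates.

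**The concern.** The protocol identifies a source of variance and then takes no step against it in the allocation or in the one analysis it describes. The allocation scheme matters most here, because it must be fixed before the first patient is enrolled and a later SAP cannot add it.

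At stake are two things. The arms may differ by chance in the share of complex operations or of older patients, which makes a small trial harder to interpret. And outcome variation due to known baseline factors stays in the error term, which costs precision. The second matters mainly for troponin I and length of stay (sections 2 and 3.1.3), which are continuous and are not among the endpoints dropped in the change of study plan.

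**Working it through.** **Inputs from the protocol (3.2.2).** "A total of 90 patients per group were estimated"; "the incidence of cognitive decline at 5-7 days postoperative is 30% after on-pump surgery"; "one-third reduction could be achieved using RIPC"; "We estimated loss to follow up as 5 % of the patients". Significance level and power are not stated; I assume two-sided 5% and 80%.

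**Inputs that are assumptions.** The protocol gives no procedure mix and no rate of postoperative cognitive dysfunction (POCD) by procedure or age. Shares and stratum risks below are therefore illustrative, and ranges are shown.

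**1. The plan's own figure.** For 30% against 20%:

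n = [1.96·√(2·0.25·0.75) + 0.842·√(0.30·0.70 + 0.20·0.80)]² / 0.10² ≈ 294 per group, and 294/0.95 ≈ 310 after 5% loss.

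The stated 90 is not reproduced. Power at 90 per group is 34%, and about 32.5% with 85.5 evaluable. This is a separate defect; here it only sets the baseline for step 4.

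**2. Chance imbalance without stratification.** Take 180 patients split exactly 90:90, with a binary factor whose count in one arm is hypergeometric.

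| Share with factor | SD of between-arm difference | P(≥10 points) | P(≥15 points) |
|---|---|---|---|
| 20% | 6.0 points | 9% | 1.5% |
| 30% | 6.9 points | 14% | 3.4% |
| 50% | 7.5 points | 18% | 5.2% |

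At a 30% share (54 patients), a difference of 10 points or more means 32 against 22, or worse.

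**3. What imbalance does to the primary estimate.** Assume 30% combined or aortic operations with POCD risk 45%, and 25% in the rest. The overall risk is 0.3·0.45 + 0.7·0.25 = 31%, close to the protocol's 30%.

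- SE of the difference in share: √(2·0.3·0.7/90) = 0.068.
- Shift in the POCD difference at one SE: 0.068·0.20 = 1.4 points. At the 95% limit: 1.96·0.068·0.20 = 2.7 points.
- Variance due to procedure class: 0.3·0.7·0.20² = 0.0084, out of 0.31·0.69 = 0.2139, or 3.9%.
- SE of the POCD difference with that variance left in: √(2·0.2139/90) = 6.9 points. With it removed: √(2·0.2055/90) = 6.8 points. The 95% half-width falls from 13.5 to 13.2 points.
- In patients: 3.9% of 180 ≈ 7.

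**4. Power, by simulation.** 200,000 trials per scenario, 85 evaluable per arm, one binary factor, one-third relative reduction; crude two-proportion test against a Mantel-Haenszel test.

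| Share; control risks | Unstratified, crude | Unstratified, adjusted | Stratified, crude | Stratified, adjusted |
|---|---|---|---|---|
| 50%; 25% / 35% | 32.8% | 32.6% | 32.8% | 32.8% |
| 50%; 20% / 40% | 32.5% | 33.3% | 32.4% | 33.4% |
| 50%; 15% / 45% | 32.6% | 34.6% | 31.9% | 34.7% |
| 30%; 22% / 48.7% | 32.4% | 33.6% | 32.1% | 34.0% |

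From the first column to the last, the gain is 0 to about 2 points, most of it from adjustment. With no treatment effect, the unstratified crude test rejects in about 5% of trials in every scenario. Stratifying and then ignoring the factor makes the crude test conservative (4.8%, 4.5%, 3.8% and 4.3% down the rows), so the analysis should account for the factor.

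**5. Continuous secondary endpoints.** Adjustment multiplies residual variance by about 1 − R². If procedure class and age explained 10% to 30% of the variance (an assumption; the protocol offers no figure), the same precision would need about 10% to 30% fewer patients.

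**The case against.** The strongest reply is that a two-arm, single-centre trial of 180 patients may legitimately randomise without strata. Chance imbalance is already reflected in the standard error, so it should not be counted again as an extra error. The primary endpoint is decline from the patient's own baseline (3.2.1.2), which removes stable differences in test level, though not differences in susceptibility to decline. On the primary endpoint the gain is worth about 7 patients. All of this stands, and it limits the point to a cheap improvement.

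A reader might infer more than the document supports:

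- **That heterogeneity is an established fact.** Section 3.2.3 says only that it might occur, and it speaks of procedures, not age. Age comes from 3.1.2.
- **That simple randomisation is planned.** The text names no scheme; it does not say that strata or blocks are absent.
- **That the primary analysis will be unadjusted.** No primary test is stated. Adjustment is neither planned nor excluded and may properly sit in the SAP. Only the secondary comparisons are described, and those as exploratory.
- **That the result would be biased, or shifted by a quarter of the planned 10-point effect.** The 2.7 points is a 95% limit on assumed inputs; one SE is 1.4 points. Over repeated randomisations the shift averages zero.
- **That procedure type is shown to predict POCD, troponin release and length of stay.** Section 3.1.2 ties complexity to morbidity and mortality in general and gives no rates by procedure.

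**Conclusion.** The point holds as a modest weakness in balance and precision. The protocol raises a variance problem, names age and complexity as drivers of morbidity, and states no design measure in response. A chance difference of 10 points or more in a factor carried by 20% to 50% of patients has probability 9% to 18%, taking the arms as exactly 90 each. The gain from acting is about 0 to 2 power points for POCD, or about 4% of the variance if stratum risks are 45% and 25%. It is possibly larger for troponin I and length of stay, by an amount the protocol does not allow one to fix. Validity is not in question. Neither stratification nor adjustment would materially change the roughly one-in-three power of the stated sample size, which needs its own correction.

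**What to change.** - **Section 3.2.1.2:** state that patients are randomised 1:1 in permuted blocks of varying size, stratified by planned procedure class (isolated CABG; isolated valve; combined or aortic).
- **Section 3.2.2, secondary endpoints:** adjust the comparisons for procedure class and age, using ANCOVA on a suitable scale for continuous outcomes such as troponin I and length of stay.
- **Section 3.2.2, primary endpoint:** state that the POCD comparison will account for the stratification factor, and leave the exact model and effect measure to the SAP.

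The cost is a three-stratum list and slightly more list administration. Planned procedure and age are both known before surgery, so no further data collection is needed.

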**3.2.4. Statement of approval**

This study will be performed in accordance with the revision of the Declaration of Helsinki (1996). Study protocol, patient information and informed consent will be send to the ethics committee of the University of Kiel and the competent authorities for appraisal.

**Changes of the study plan (date 01/01/2009)**

Due to technical limitations, lack of financial resources and lack of human resources the following endpoints will not be investigated:

- Cardiac performance analysed by echocardiography
- Cardiac performance analysed by cardiac MRI
- Serum inflammatory biomarkers (CrP, cytokines, chemokines)
- Transcriptional profiling with microarrays of leukocyte gene expression 24 hours after surgery
